### Participants:

The study population will consist of women aged 30–65 years who are hrHPV-positive for non-HPV16/18 types following primary HPV DNA testing during routine cervical cancer screening. Inclusion criteria will include laboratory confirmation of hrHPV infection with one or more non-HPV16/18 types (e.g., 31, 33, 35, 39, 45, 51, 52, 56, 58, 59, 66, or 68) using the validated Xpert^®^ HPV platform, age 30–65 years, and willingness to provide written informed consent and comply with study follow-up. Exclusion criteria will include the detection of HPV16 and/or HPV18 infection (triaged per standard-of-care protocols), previous diagnosis of CIN2+, cervical cancer, or history of hysterectomy, current pregnancy, immunosuppression unrelated to HIV, or prior HPV vaccination, and inability to provide informed consent or complete study procedures.

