### Study endpoints:

The primary endpoint is the proportion of histologically confirmed CIN2 + lesions in each study arm, and the secondary endpoints are (1) diagnostic performance metrics (sensitivity, specificity, PPV, NPV) of the risk-stratified algorithm versus cytology for CIN2 + detection; (2) referral rates for colposcopy following triage in each arm; (3) colposcopic yield, defined as the proportion of referred women with histologically confirmed CIN2+; and (4) clinical and demographic predictors of CIN2+.

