### Sample size calculation:

Sample size was calculated based on the primary objective of testing the non-inferiority of the risk-stratified algorithm compared with cytology-based triage for detecting CIN2+. Assuming a CIN2 + detection rate of 94% for cytology-based triage [14], a non-inferiority margin of 10%, a one-sided alpha of 5%, a power of 80%, and accounting for a 5% non-response or missing data rate, we estimate that n = 148 non-16/18 HPV-positive women (74 per arm) will be required to detect non-inferiority. This sample size will also provide > 80% power to detect a 20% relative reduction in unnecessary referrals (secondary endpoint) between study arms.

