### Study procedures, randomization, and blinding:

The study investigators will screen and identify eligible non-HPV16/18-positive women for the study. Eligible women will be invited to participate in the study after receiving a comprehensive explanation of its purpose, procedures, potential risks and benefits, and will provide written informed consent before enrolment. Once consent is obtained, an interviewer-administered questionnaire will be applied to obtain baseline information on sociodemographic characteristics, reproductive and sexual history, and HIV and HPV status using the electronic case report form (eCRF) on the REDCap database hosted on a secure CMUL server with audit trails and user authentication. Eligible participants will then be randomized 1:1 using a computer-generated permuted block randomization sequence (block sizes of 4–6) stratified by age (< 35 vs ≥ 35 years) and HIV status [Figure 1]. Allocation concealment will be maintained using sequentially numbered, opaque, sealed envelopes prepared and safeguarded by an independent trial statistician.

**Intervention arm (risk-stratified triage)**: Participants will undergo triage using a risk-stratified algorithm incorporating a composite of readily available clinical and demographic data, including older age ≥ 35 years, HIV seropositivity with CD4 < 200 cells/mm^3^, cigarette smoking, long-term oral contraceptive use > 5 years, and multiple hrHPV genotype infections, to identify women at the highest risk of CIN2+ [15, 16]. Women with any of these risk factors will be referred for colposcopy, while those without will undergo repeat testing at 12 months.**Control arm (cytology-based triage)**: Participants will undergo reflex cytology (Pap test) interpreted per the Bethesda 2014 classification [17]. Women with atypical squamous cells of undetermined significance (ASC-US) or higher will be referred for colposcopy; those with normal cytology will undergo repeat testing at 12 months.

Colposcopy and biopsy will be performed for all screen-positive women in both arms. Histopathologic diagnosis (CIN1, CIN2, CIN3, or carcinoma) will be confirmed by two independent pathologists blinded to group allocation. Blinding of participants and clinicians is not feasible due to the procedural nature of triage methods; however, laboratory personnel and outcome assessors (cytologists, pathologists, and data analysts) will remain blinded to group allocation.

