### Statistical analysis plan:

All analyses will follow the intention-to-treat (ITT) approach, supplemented by per-protocol sensitivity analyses. Descriptive statistics will summarise participant characteristics. The primary endpoint (CIN2 + detection) will be compared between arms using the proportional difference with corresponding 95% confidence intervals (CI). Non-inferiority will be concluded if the lower bound of the 95% CI for the difference (risk-stratified – cytology) is above the pre-specified non-inferiority margin (–10%). Referral rates, colposcopic yield and diagnostic performance metrics will be compared using chi-square or Fisher’s exact tests. ROC curve analysis will assess the discriminative performance of the triage methods. Logistic regression will be used to identify independent predictors of CIN2+, adjusting for age, HIV status, parity, and other covariates. Missing data will be handled using multiple imputation, assuming data are missing at random [18]. All analyses will be conducted using Stata version 18 (StataCorp LLC, Texas, USA).

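### The claim of more than 80% power for a 20% relative reduction in unnecessary referrals holds, per randomised woman, only if about 85% to 90% of control women are referred unnecessarily

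*Protocol article*

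**What the plan says.** The sample size section derives 148 women from the primary non-inferiority comparison. Its inputs are a "detection rate of 94% for cytology-based triage", a 10% margin, "a one-sided alpha of 5" per cent, 80% power and 5% missing data. It then adds that the same number gives more than 80% "power to detect a 20% relative reduction in unnecessary referrals (secondary endpoint) between study arms". No control rate, denominator or alpha is attached to that second statement.

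The endpoints section lists referral rates in each arm and, separately, "colposcopic yield, defined as the proportion of referred women with histologically confirmed" CIN2+. The statistical analysis section says: "Referral rates, colposcopic yield and diagnostic performance metrics will be compared using chi-square" or Fisher's exact tests, without giving sidedness.

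For the intervention arm, the procedures section builds the algorithm from "readily available clinical and demographic data, including older age" of at least 35 years, advanced HIV disease, smoking, long oral contraceptive use and multiple genotypes. The rule is: "Women with any of these risk factors will be referred for colposcopy, while those without will undergo repeat testing at 12 months". On eligibility: "The study population will consist of women aged 30–65 years".

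**The concern.** A sample size chosen for a 10-point margin around a 94% proportion does not automatically give good power for a relative change in some other proportion. A 20% relative reduction is a small absolute difference unless the starting rate is high: 6 points from 30%, 10 points from 50%, 18 points from 90%. With 74 women per arm only the last of these is within reach.

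The Introduction's central hypothesis has two halves, comparable sensitivity and fewer unnecessary colposcopies, and the power sentence tells the reader that the trial can show the second. If it cannot, a non-significant referral comparison may be reported as good evidence of no difference when it is merely uninformative.

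**Working it through.** **Primary figure first.** n per arm = (1.645 + 0.842)² × 2 × 0.94 × 0.06 / 0.10² = 69.7, rounded up to 70. Then 70/0.95 = 73.7, rounded up to 74, or 148 in total. The stated number reproduces.

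**Secondary claim, per randomised woman.** Inputs from the article: n = 74 per arm and p2 = 0.8 × p1. The control rate p1 is not given, so it is varied. Sidedness is not given for this test, so both are shown at 5%. With pooled p = (p1 + p2)/2:

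power = Φ{ [p1 − p2 − z√(2p(1−p)/n)] / √([p1(1−p1) + p2(1−p2)]/n) }

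Example at p1 = 0.50, p2 = 0.40, p = 0.45: the null standard error is √(0.495/74) = 0.0818 and the alternative standard error is √(0.49/74) = 0.0814. Two-sided: (0.10 − 1.96 × 0.0818)/0.0814 = −0.74, so power is 0.23. One-sided: (0.10 − 1.645 × 0.0818)/0.0814 = −0.42, so power is 0.34.

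| Control rate | Power, two-sided | Power, one-sided | n per arm for 80% (two-/one-sided) |
|---|---|---|---|
| 30% | 0.127 | 0.205 | 859 / 676 |
| 50% | 0.229 | 0.336 | 388 / 305 |
| 80% | 0.584 | 0.702 | 123 / 97 |
| 90% | 0.803 | 0.881 | 74 / 58 |

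Solving for 80% power gives a control rate of 89.9% two-sided or 85.5% one-sided. With 70 evaluable per arm these become 90.8% and 86.6%. Full enumeration of the two binomials for the named tests agrees. Chi-square power is 0.818 two-sided at 90% and 0.797 one-sided at 85%. Two-sided Fisher's exact test gives 0.752 at 90% and 0.81 at 92%.

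**If the denominator is referred women only.** 'Unnecessary' would then be one minus the colposcopic yield. If every woman in both arms were referred, the calculation above applies unchanged. If fewer are referred, the required rate rises. Taking the most favourable intervention arm (all 74 referred), the same formula with unequal arms gives the share of referred controls who must lack CIN2+ for 80% power:

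- cytology refers 70% (about 52 women): 89.4% one-sided, 93.4% two-sided
- cytology refers 50% (37 women): 93.1% one-sided, 96.7% two-sided
- cytology refers 30% (about 22 women): 98.1% one-sided, not reachable two-sided

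So 80% needs nearly all referred controls to be free of CIN2+ and cytology to refer a large share of women.

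**Age rule (supporting remark, conditional on the age mix).** Let s be the share of recruits aged 35 or over and p the CIN2+ prevalence, equal in both arms. Every intervention woman aged 35 or over is referred. Unnecessary referrals per woman are therefore at least the share aged 35 or over without CIN2+, which is s − p or more. A 20% reduction needs a control rate of at least (s − p)/0.8. Neither s nor p is given for this population. Assuming p = 5.6%, the 12-month risk that the Introduction cites for other high-risk types, the control rate must be at least:

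- s = 50%: 0.444/0.8 = 55.5%
- s = 60%: 0.544/0.8 = 68.0%
- s = 70%: 0.644/0.8 = 80.5%
- s = 80%: 0.744/0.8 = 93.0%

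**The case against.** The best defence is that this is a condensed article of a longer protocol, and that the assumptions behind a secondary power statement may well be in the full document. That stands as far as missing detail goes: leaving out the control rate would not by itself be a finding. But the article publishes a numerical property of the design, and that number can be checked against 74 per arm over every possible control rate. It is met only at the top of the range.

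A second defence is that the sentence has not been shown to be false. That is correct. No document figure says which control rate was assumed or how often cytology will be ASC-US or worse here, so calling 85% to 90% unlikely is a judgement. It would mean that nearly all control women have abnormal cytology without CIN2+, which leaves little room for triage.

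Third, the age rule is openly stated. A reader might infer that the protocol conceals that all women aged 35 or over are referred, but the procedures section says so and randomisation is stratified at that age. A reader might also infer that a reduction is impossible once more than 80% of recruits are 35 or over. That limit applies to all referrals. For unnecessary referrals it moves to 0.8(1 − p) + p, about 81% at p = 5.6%, and if the denominator is referred women the age rule sets no direct limit. Without the age mix, the documents do not support saying that the algorithm cannot reduce unnecessary referrals.

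**Conclusion.** The concern holds for the power sentence. Per randomised woman, the claim is true only at control rates of about 85.5% or more (one-sided 5%) or 89.9% or more (two-sided 5%). At 30% to 80%, power runs from 0.13 to 0.58 two-sided and from 0.21 to 0.70 one-sided. The referred-women reading does not relax this. These results rest on 74 per arm, a reduction that is relative as written, and a 5% test; only the control rate and denominator are open.

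The age rule adds a conditional point: if most recruits are 35 or older, a 20% reduction may be hard to achieve at all, whatever the power.

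A reader might go further and say that the 94% refutes the claim, because 94% of women with CIN2+ found leaves at most 6% referred unnecessarily. The article does not settle what the 94% is a proportion of, so that inference is not drawn here. Nor does anything here touch the primary sample size. This is a correction to a secondary claim, but one that bears on half of the central hypothesis.

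**What to change.** Delete the secondary power sentence, or restate it with:

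- the definition and denominator of an unnecessary referral
- the assumed control rate and its source
- the alpha and sidedness
- the power that 74 per arm gives under those assumptions

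Where that power is below 80%, describe the referral comparison as not powered and to be read from its estimate and confidence interval. If a 20-point absolute reduction was meant, say so. Power would then be about 0.79 to 0.93 one-sided, or 0.69 to 0.87 two-sided, for control rates from 30% to 90%, so the claim would still depend on the rate.

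The sample size, primary analysis and triage rule do not change. The Study Status section says that recruitment has not begun, so the edit can be made before enrolment. The cost is a few words and a more modest secondary claim.

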### Study procedures, randomization, and blinding:

The study investigators will screen and identify eligible non-HPV16/18-positive women for the study. Eligible women will be invited to participate in the study after receiving a comprehensive explanation of its purpose, procedures, potential risks and benefits, and will provide written informed consent before enrolment. Once consent is obtained, an interviewer-administered questionnaire will be applied to obtain baseline information on sociodemographic characteristics, reproductive and sexual history, and HIV and HPV status using the electronic case report form (eCRF) on the REDCap database hosted on a secure CMUL server with audit trails and user authentication. Eligible participants will then be randomized 1:1 using a computer-generated permuted block randomization sequence (block sizes of 4–6) stratified by age (< 35 vs ≥ 35 years) and HIV status [Figure 1]. Allocation concealment will be maintained using sequentially numbered, opaque, sealed envelopes prepared and safeguarded by an independent trial statistician.

**Intervention arm (risk-stratified triage)**: Participants will undergo triage using a risk-stratified algorithm incorporating a composite of readily available clinical and demographic data, including older age ≥ 35 years, HIV seropositivity with CD4 < 200 cells/mm^3^, cigarette smoking, long-term oral contraceptive use > 5 years, and multiple hrHPV genotype infections, to identify women at the highest risk of CIN2+ [15, 16]. Women with any of these risk factors will be referred for colposcopy, while those without will undergo repeat testing at 12 months.**Control arm (cytology-based triage)**: Participants will undergo reflex cytology (Pap test) interpreted per the Bethesda 2014 classification [17]. Women with atypical squamous cells of undetermined significance (ASC-US) or higher will be referred for colposcopy; those with normal cytology will undergo repeat testing at 12 months.

Colposcopy and biopsy will be performed for all screen-positive women in both arms. Histopathologic diagnosis (CIN1, CIN2, CIN3, or carcinoma) will be confirmed by two independent pathologists blinded to group allocation. Blinding of participants and clinicians is not feasible due to the procedural nature of triage methods; however, laboratory personnel and outcome assessors (cytologists, pathologists, and data analysts) will remain blinded to group allocation.

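### Printed small blocks and envelope allocation, in an open-label single-site trial with a judgement-based exclusion, leave the next arm partly foreseeable; selective enrolment is possible but not shown, and cheap to guard against before recruitment

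*Protocol article*

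**What the plan says.** Under Study procedures, randomization, and blinding, the protocol article sets this sequence: "The study investigators will screen and identify eligible non-HPV16/18-positive women for the study"; consent follows; a baseline questionnaire is entered in REDCap, covering sociodemographic data, reproductive and sexual history, and HIV and HPV status; and "Eligible participants will then be randomized 1:1". The sequence is a "computer-generated permuted block randomization sequence (block sizes of 4–6) stratified by age (< 35 vs ≥ 35 years) and HIV status". Concealment is by "sequentially numbered, opaque, sealed envelopes prepared and safeguarded by an independent trial statistician". On masking, the same section states: "Blinding of participants and clinicians is not feasible due to the procedural nature of triage methods". Laboratory staff, pathologists and data analysts stay blinded.

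Under Participants, one exclusion is "inability to provide informed consent or complete study procedures", and willingness to comply with follow-up is an inclusion criterion. Study Design and Settings names one hospital. In the intervention arm any single risk factor, including age 35 or over, leads to colposcopy. Study Status says that recruitment has not begun.

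**The concern.** Each feature is common alone. Together they leave a route for selection bias. Past allocations are visible to clinicians at one site. The block sizes are small and printed, so the arm that is behind in a stratum is the better guess for the next woman. The people who enrol also decide whether a woman is able to complete the procedures. Before allocation they know her age, HIV status and HPV status, and so part of her risk.

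The primary endpoint is the proportion of women in each arm with histologically confirmed CIN2+, compared as a risk difference. If who is enrolled depended on the expected arm, the arms would differ in underlying risk and that difference would enter the primary comparison. Concealing each envelope's contents does not remove this route, because the guess comes from earlier allocations.

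**Working it through.** **Inputs.** From the protocol article: 1:1 allocation; block sizes 4–6, read as 4 and 6 because an odd block cannot be balanced; four strata (two age groups by HIV status); 148 women. The article gives no guess rate. Its sample size, used here as the number of allocations, reproduces: (1.645 + 0.842)² × 2 × 0.94 × 0.06 / 0.10² = 69.7, so 70 per arm; 70 / 0.95 = 73.7, so 74 per arm and 148 in all.

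Assumed: staff guess the arm that is behind in the stratum and toss a coin when the arms are level. The mix of women across strata is not given; equal strata and a 72/18/8/2% split were both tried.

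**Guess rate in a full block of size n.** Expected correct guesses = n/2 + (2ⁿ / C(n, n/2) − 1)/2.
- n = 4: 2 + (16/6 − 1)/2 = 2.833, or 70.8%.
- n = 6: 3 + (64/20 − 1)/2 = 4.1, or 68.3%.
- Equal mix of the two: (2.833 + 4.1)/10 = 69.3%.
- Simulation of 148 women in four strata with unfinished last blocks: about 69% under either stratum mix.

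**How far this depends on a complete tally** (simulated, blocks of 4 and 6, 72/18/8/2% split).

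| What staff track | Correct guesses |
|---|---|
| Every past allocation, by stratum | 69% |
| 10% of past allocations missed | 60% |
| 25% missed | 56% |
| 50% missed | 54% |
| One tally across all strata | 60% |

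**Allocations known with certainty.** With one fixed, known size the share is 1/(n/2 + 1): 33% for 4 and 25% for 6. With 4 and 6 mixed at random it is about 6%.

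**What other schemes would do** (complete tally, long-run rates).
- Blocks of 2, 4, 6 and 8: (1.5 + 2.833 + 4.1 + 5.329)/20 = 68.8%; about 68% in simulation. Almost no gain, and the second allocation in a block of 2 is always forced.
- Blocks of 6, 8, 10 and 12: (4.1 + 5.329 + 6.532 + 7.716)/36 = 65.8%, or about 66%.
- Big-stick design with limit 3 (a fair coin unless the arms differ by 3): the imbalance sits at the limit 1/6 of the time, so the rate is 1/2 + (1/2)(1/6) = 58.3%.

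**What steering could do to the result (illustration only).** The article's Introduction gives a 12-month CIN2+ risk of 5.6% for other high-risk types. The sample size section instead assumes a 94% detection rate. If 5.6% applied, each arm of 74 would expect 74 × 0.056 = 4.1 cases. With 4 cases in each arm, the Wald 95% lower bound is −7.3%; with 4 in the intervention arm and 6 in control it is −10.8%. Two cases would then cross the −10% margin. But replacing an average woman with one at double the risk adds only 0.056 expected cases, so one extra case takes about 1/0.056 = 18 such replacements, and two take about 36.

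**The case against.** The strongest reply is that the 69% belongs to stratified permuted blocks in general and needs a complete tally by stratum, which the article nowhere says recruiters keep. This stands: 69% is a ceiling.

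Safeguards also deserve credit. An independent statistician prepares and keeps the envelopes. The baseline form precedes randomisation and sits in REDCap with audit trails. Independent monitors review enrolment logs and protocol deviations (Quality control and data monitoring). These limit early opening and leave a trail. They do not stop prediction from visible past allocations, and the article does not say that eligibility is fixed irrevocably before release.

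Three stronger readings are tempting, and the document does not support them.
- *Staff already hold every input to the algorithm.* CD4 count and smoking are not named among the baseline items. Every woman aged 35 or over is algorithm-positive, so in those strata referral status gives no basis for choosing between women.
- *Steering a handful of women would reverse the conclusion.* Staff would be steering on risk, not on histology, and the illustration needs dozens of replacements for two cases. No bias in the primary difference has been shown.
- *The range 4–6 means that blocks of 5 will be used.* It is ordinary shorthand for 4 and 6.

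The article condenses a fuller protocol that may hold more operational detail. The point therefore rests on what the article does fix: the printed sizes, the envelopes and the judgement-based exclusion.

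**Conclusion.** The concern holds as a foreseeability risk that is cheap to reduce, not as a demonstrated bias. Guessing reaches at most about 69%, on the assumptions that staff see and tally every allocation in each stratum and that blocks of 4 and 6 are mixed at random. With modest gaps in the tally it is 56% to 60%. The document gives no evidence that anyone would steer enrolment, and the effect on the primary difference cannot be sized from it. The case for acting is that recruitment has not started and REDCap is already in use.

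**What to change.** - Require eligibility, including the judgement on completing procedures, to be recorded irrevocably and the baseline risk-factor form completed in REDCap before allocation is released. This matters most, because changing the block sizes alone moves the guess rate only a little.
- Release allocation from REDCap instead of from envelopes.
- Log every exclusion after consent, with its reason and whether allocation was known, for the monitors to review.
- Delete the block sizes from the protocol text and state that the scheme is known only to the independent statistician. Keep the same strata.
- Do not use 2, 4, 6 and 8. Use larger even blocks (6 to 12, about 66%) or an imbalance-limited scheme such as the big-stick design with limit 3 (about 58%). Because about one allocation in six is forced at that limit, the limit must stay undisclosed too.

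The cost is a short protocol edit, some set-up in an existing system, and slightly looser balance between arms in small strata.

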## Methodology

### Study Design and Settings:

This study (*STRAT-CIN Trial*) proposes a two-arm, parallel, open-label, non-inferiority randomized controlled trial among sexually-active women at the Cytology and Colposcopy clinics of the Lagos University Teaching Hospital (LUTH), Nigeria, between June 2026 and January 2027. LUTH is the foremost healthcare institution in Lagos and serves as a referral centre for other government-owned and private hospitals in Lagos and its neighbouring states. The hospital provides a variety of care, including integrated gynecologic oncology prevention services such as Pap smearing, HPV testing and colposcopy services, including biopsy and histology. Laboratory analyses will be performed at the Department of Anatomic and Molecular Pathology (AMPATH), College of Medicine, University of Lagos, equipped with facilities for cytology, histopathology, and HPV genotyping [13].

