## Study Status

At the time of manuscript submission, participant recruitment for the trial has not yet commenced. Enrollment is planned to begin in July 2026, with recruitment expected to be completed by January 2027, when the final participant will be enrolled. This manuscript describes Version 4.0 of the study protocol, dated 17 June 2026.

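### Sensitivity, specificity, NPV and ROC are promised, but only triage-positive women get histology, so these absolute measures are not identified

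*Protocol article*

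**What the plan says.** All places are in the protocol article.

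- **Who gets histology** (Study procedures, randomization, and blinding): "Colposcopy and biopsy will be performed for all screen-positive women in both arms".
- **Triage-negative women, intervention arm** (same section): "Women with any of these risk factors will be referred for colposcopy, while those without will undergo repeat testing at 12 months".
- **Triage-negative women, control arm** (same section): "those with normal cytology will undergo repeat testing at 12 months".
- **First secondary endpoint** (Study endpoints): "diagnostic performance metrics (sensitivity, specificity, PPV, NPV) of the risk-stratified algorithm versus cytology".
- **Analysis** (Statistical analysis plan): the metrics are compared by chi-square or Fisher's exact tests, and "ROC curve analysis will assess the discriminative performance of the triage methods". Missing data are to be multiply imputed under a missing-at-random assumption.
- **Hypothesis** (Introduction): the algorithm is expected to match cytology on sensitivity with fewer unnecessary referrals.
- **Dates**: Study Design and Settings places the trial "at the Cytology and Colposcopy clinics of the Lagos University Teaching Hospital (LUTH), Nigeria, between June 2026 and January 2027". Study Status says "Enrollment is planned to begin in July 2026, with recruitment expected to be completed by January 2027, when the final participant will be enrolled".

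No endpoint or analysis uses the 12-month results. No sample of triage-negative women is verified, and no correction for partial verification is described.

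**The concern.** Sensitivity, specificity and NPV all need disease status in women whom the triage method calls negative. The verification rule withholds histology from exactly those women in each arm. The endpoint list and the verification rule therefore conflict inside the document, and an analysis plan cannot recover outcomes that the design does not collect.

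The risk is a falsely reassuring result. Under the two simplest codings, both arms show 100% sensitivity, and a Fisher test then compares 100% with 100%. A reader could take that as evidence that a triage rule which misses precancer is as accurate as cytology.

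**Working it through.** **1. The plan's own figure.** Inputs from Sample size calculation: 94% in both arms, margin 10 points, one-sided alpha 5%, power 80%, 5% loss.

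n = 2 × 0.94 × 0.06 × (1.645 + 0.842)² / 0.10² = 69.7, so 70 per arm. Then 70 / 0.95 = 73.7, so 74 per arm and 148 in total. The stated size reproduces and is not at issue here.

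**2. What is observed in each arm.** Let TP and FP be referred women with and without CIN2+, and FN and TN be triage-negative women with and without CIN2+. Histology gives TP and FP. For the arm's own triage method, FN and TN are not separated.

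| Handling of unbiopsied women | Sensitivity | Specificity | NPV |
|---|---|---|---|
| Left out (verified women only) | TP/(TP+0) = 100% | 0/(0+FP) = 0% | 0/0, undefined |
| Counted as disease-free | TP/(TP+0) = 100% | (TN+FN)/(TN+FN+FP) | 100% |

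**3. Example.** 74 women and prevalence 5.6% (the 12-month CIN2+ risk for other hrHPV types quoted in the Introduction). True sensitivity 40% and true specificity 70% are assumptions.

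- CIN2+: 74 × 0.056 = 4.14. TP = 1.66, FN = 2.49.
- No CIN2+: 69.86. FP = 20.96, TN = 48.90.
- Counted as disease-free: sensitivity reads 100% (true 40%), NPV reads 100% (true 48.90/51.39 = 95.2%), specificity reads 51.39/72.34 = 71.0% (true 70%).

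The same holds over a grid of 24 assumed scenarios (prevalence 5.6%, 10% or 19.5%; sensitivity 40%, 60%, 80% or 94%; specificity 30% or 70%): sensitivity reads 100% in every one under either coding. In the most extreme (19.5%, 40%, 30%), the true NPV is 67.4% and still reads 100% under the second coding.

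**4. ROC.** For the binary refer/do-not-refer result, the curve among verified women is degenerate, because all of them are positive. A curve over cytology grade or number of risk factors could be drawn among referred women. It is conditional on referral and is not the ROC of the triage method.

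**5. Imputation.** Control women with normal cytology are never verified, and women negative on both methods are verified in neither arm. Any imputed histology for them is extrapolated from referred women.

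**6. Timing.** Enrolment from July 2026 to January 2027 puts the repeat tests between July 2027 and January 2028. That is after January 2027, unless follow-up runs longer than the stated trial dates.

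**7. What randomisation does identify.** Detection per woman randomised equals prevalence × sensitivity. Prevalence is equal in expectation between arms, so the ratio of detection proportions estimates the ratio of sensitivities. This takes attendance and the yield of colposcopy and biopsy as equal between arms. Likewise, the ratio of proportions referred without CIN2+ estimates the ratio of false-positive fractions. Example at 5.6% prevalence: true sensitivities of 40% and 80% give 1.66 and 3.32 detected, ratio 0.50, which is correct, while both naive sensitivities read 100%.

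**8. Precision of the ratio.** Assume 4 of 74 detected per arm. SE(log ratio) = √(1/4 − 1/74 + 1/4 − 1/74) = 0.688. 95% CI = exp(±1.96 × 0.688) = 0.26 to 3.9.

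**The case against.** **A reader might infer that sensitivity is 100% by construction.** The document does not fix this. It follows only if verified women alone are analysed or unbiopsied women are coded disease-free, and the plan states neither. Imputation would give a lower figure, though an extrapolated one.

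**A reader might infer that no false negative or true negative is ever seen.** That is too strong for the algorithm. Baseline data are collected before randomisation. If they include every item of the algorithm, its result can be derived for control women. Control women who are algorithm-negative but have ASC-US or worse get histology, so some algorithm false negatives and true negatives are observable. The groups in step 5 of the working are still never verified.

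**A reader might infer that the repeat tests certainly fall outside the trial.** Study Status dates the end of recruitment, not of follow-up, and Participants refers to study follow-up. The full protocol may run longer. The firmer point is that no endpoint or analysis uses the 12-month results, and a repeat test is not histology.

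**A reader might infer that imputation will fill the unbiopsied women and inflate detection.** The 5% allowance for non-response or missing data suggests that the authors do not regard them as missing. The wording leaves it open and should be made explicit.

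**Screen-positive could mean every HPV-positive woman.** In that case all would be verified. This contradicts the referral rules in the same section and would empty the referral-rate endpoint of meaning. The term should be clarified.

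**Conclusion.** The point stands in a bounded form. Absolute sensitivity, specificity and NPV, and the ROC of each triage method, are not identified from the verification rule as written. The hidden error can be large: in the example, a true sensitivity of 40% reads 100%. That rests on an assumed sensitivity and specificity and on one of the two simple codings. The conclusion that the measures are not identified rests on none of these assumptions, only on reading screen-positive as triage-positive.

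The defect concerns the first secondary endpoint and the ROC analysis. PPV, referral rate, colposcopic yield and the primary detection comparison are not affected by it. It would go too far to say that the central hypothesis cannot be addressed: comparable sensitivity is a relative claim, and randomisation supports a relative answer, though an imprecise one at this sample size. Study Status says that recruitment had not begun at submission, so the text can be corrected before any data exist.

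**What to change.** 1. In Study endpoints and Statistical analysis plan, delete absolute sensitivity, specificity, NPV and the ROC analysis.
2. Replace them with the following, each with a confidence interval:
   - relative sensitivity: the ratio of CIN2+ detection proportions per woman randomised;
   - relative false-positive fraction: the ratio of the proportions randomised who are referred without CIN2+;
   - PPV.
3. State that the ratios will be imprecise, citing the 0.26 to 3.9 interval for an assumed 4 of 74 detected per arm.
4. State that histology not sought because triage was negative is not treated as missing data and is not imputed.
5. Where the algorithm's items are recorded for control women, report how many cytology-detected CIN2+ the algorithm would not have referred.
6. Clarify that screen-positive means triage-positive.
7. Optionally, report the already planned 12-month results descriptively if data capture is extended. The last test would fall in January 2028, so capture would have to run past that month to include its result.

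The cost of items 1 to 6 is wording and a few further analyses, with no added biopsies or visits. Item 7 adds about 12 months of data capture or somewhat more. It would not make verification complete, because a repeat test is not a reference standard.
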